In light of key recommendations consistent across guidelines from many countries [16-19], and in a manner similar to the work of Rainville et al [109] with US physicians and Bishop and Foster [49] with UK physiotherapists, the primary questions relating to the vignette were designed to explore practitioner recommendations for patient behaviour in relation to (i) Work, (ii) Activity, and (iii) Bed-rest. Other secondary questions were added to explore investigations (including x-rays) and initial treatment interventions (e.g. advice, manual therapy, electrotherapy and exercise). The format chosen to capture responses to each of these primary questions was a 5-point Likert-type scale (Figure 3), based on questions originally used by Rainville et al [109].

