**Figure 3 F3:**
[figure not shown]
**Questions and corresponding response options relating to a low back pain patient vignette **The points of dichotomisation for each scale, based on expert consensus, are shown (with arrows). For each scale, the response option(s) to the right of each arrow were interpreted as consistent with guideline recommendations. The numbers above and between response options represent the frequency of expert opinion for the point of dichotomy relating to that scale. Lenient interpretations (L) are placed on the top row above response options, and strict interpretations (S) on the bottom row. The five-point scales are considered ordinal. However, two items of the scale related to Work will be combined (highlighted in bold italics) to form a four-point scale in this case.

In order to inform the analysis of the results, and as the responses to these questions were being interpreted in light of guideline recommendations, an expert consensus exercise was performed. A group of 12 experts with extensive prior experience in LBP research were contacted independently and provided with a copy of the vignette and questions. Feedback from the experts confirmed that the five-point scales could be considered ordinal. However, it was recommended that two items of the scale related to Work should be combined (highlighted in bold italics in Figure 3) to form a four-point scale in this case.

There are two research questions relating to the primary outcome of reported behaviour. Each of these requires a different analysis to test for a statistically significant change between the two arms of the trial at the six-month post-intervention time-point. The two research questions are:

1. For each scale, can the intervention change the response proportions of 'guideline-consistent' and 'guideline-inconsistent' reported behaviour?

2. For each scale, can the intervention change the response proportions of reported behaviour across the entire range of responses?

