The first of these questions represents the primary outcome measure for this study. It relates to changes in the proportions of responses either side of a predetermined cut-off point for each reported behaviour research question. Therefore, each of the original five-point scales will be dichotomised to create a new variable with categories defined as 'guideline-consistent' and 'guideline-inconsistent'. The location of the cut-off points for each scale is based on the expert consensus exercise. All experts were asked to give, where possible their 'lenient' and 'strict' interpretation of internationally agreed recommendations from primary care and occupational evidence-based guidelines [16-19] for each scale. These two interpretations will allow for a sensitivity analysis.

The wording and points of dichotomisation for each scale question are shown (with arrows) in Figure 3. For each scale, the response option(s) to the right of the arrow were interpreted as recommendations consistent with those of the guidelines. The positions of the red arrows indicate the location of cut-off points for the most frequent 'strict' expert interpretation of the guideline recommendations. The blue arrows indicate the location of cut-off points for the most frequent 'lenient' expert interpretation.

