### Sample size calculation

The primary outcome measure for this trial was the proportion of 'guideline-consistent' and 'guideline-inconsistent' reported behaviour, relating to the patient vignette for the key variables of work, activity, and bed-rest (Figure 3). This analysis is also in need of more statistical power than the alternative analysis using change in responses across the whole scale. It is therefore the appropriate criterion by which to estimate the target sample size for the trial. In light of previous studies on practitioner behaviour change [59,73], we defined a change of 10% in reported behaviour between the proportions of practitioners from baseline to the six-months post-intervention follow-up as a clinically meaningful change. Thisdifference is the same as the median effect size reported in a review of guideline implementation studies reported in a subsequent review [61,63].

There are no existing data on 'guideline consistent' responses on which we could base our sample size calculation. To show a 10% difference in the proportion of these practitioners who, at the six-month post-intervention follow up, would give 'guideline consistent' responses to this questionnaire, the greatest statistical power is needed when proportions in each group are 45% and 55%. To show this difference at the 5% significance level with 90% power, valid data from at least 543 participants in each arm of the trial are needed for analysis (1086 total). Previous studies using a similar questionnaire format to measure outcomes have shown a response rate of between 31% and 65% [10,41,73,109,115]. Based on these figures, and the overall response rate of the pilot study, a recruitment rate of approximately 50% was anticipated at baseline. Allowing for 40% loss to follow-up, 900 practitioners had to be recruited into each arm of the trial at baseline (1800 total). Further allowing for the estimated recruitment rate of 50% at baseline, approximately 3600 practitioners needed to be invited to participate at the start of the study. A total of 3604 were actually invited. Such over-sampling strategies are typical of studies on healthcare practitioners based on survey methodology [e.g. [41,115]].

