### Data handling and analyses

The anonymised questionnaire data have been transferred into electronic format using a pre-coded datafile via Statistical Package for Social Scientists (SPSS) Data Entry (version 3.0) software, which is designed to reduce systematic errors during data entry. Data were independently entered by an experienced data entry administrator, who was blind to the participant identities. For purposes of reducing error, 20% of all data entered in the SPSS datafile was checked by one of the research team, blind to participant intervention allocation at the time.

As this is a pragmatic trial, the primary analysis will be performed on an intention to treat basis, as recommended by Bland [71]. It will include all participants randomised, even if they did not subsequently receive or read the intervention package when allocated. A proposed secondary analysis will focus on participants who appear to have read the information package, as identified by means of responses to a question on the follow-up questionnaire acting as a proxy. Data will be analysed using SPSS (version 11.5). All significance tests will be two-sided and statistical significance will be set at the 5% level.

The reported behaviour outcomes require a different analysis for each of the two research questions. The dichotomous variable, with categories defined as either 'guideline-consistent' or 'guidelineinconsistent', will be analysed using a binomial regression model (primary analysis). This will allow for between-arm differences of the proportions of responses that fall within each category at follow-up to be tested. The points of dichotomy will be based on the 'lenient interpretation' for each variable, as per the expert consensus exercise (Figure 3). The 'strict interpretation' for each variable will be used to provide sensitivity analyses. The original ordinal data will be analysed using an ordinal regression model, in which between-arm differences of proportions across all follow-up reported behaviour data may be tested. Baseline reported behaviour responses will be included in each model as a covariate. The secondary clinical and demographic data collected at baseline will be inspected and will also be included as covariates in the analyses, depending on the proportions of variance shared between these variables.

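### Three co-primary scales are each tested at an unadjusted 5% with no rule for the overall conclusion, so neither an any-scale nor an all-scales claim has both the stated 5% error and the stated 90% power

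*Protocol article*

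**What the plan says.** All references are to the protocol article.

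- **Three primary questions.** Under Outcome measure 1 (Reported behaviour), the primary vignette questions concern "patient behaviour in relation to (i) Work, (ii) Activity, and (iii) Bed-rest".
- **Asked per scale.** Research question 1 in the same section reads "For each scale, can the intervention change the response proportions of 'guideline-consistent' and 'guideline-inconsistent' reported behaviour". The article then adds: "The first of these questions represents the primary outcome measure for this study".
- **Confirmed in the sample size section.** The primary outcome is described there as "relating to the patient vignette for the key variables of work, activity, and bed-rest".
- **Analysis.** Data handling and analyses labels the binomial regression of the dichotomised variable as the primary analysis, with the lenient cut-off applied to each variable. It sets the level for every test: "All significance tests will be two-sided and statistical significance will be set at the 5% level".
- **Sample size.** One comparison of 45% with 55% is considered: "at the 5% significance level with 90% power, valid data from at least 543 participants in each arm of the trial are needed".
- **Aim.** The end of the Background and the Conclusion pose one effectiveness question about the package in the combined professional groups.

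The article names no lead scale, defines no composite of the three, does not say how many scales must reach significance, and makes no adjustment to the 5% level.

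**The concern.** The trial will produce three primary p-values and is meant to yield one answer. With no linking rule, the authors could report that the package changes behaviour after one scale out of three falls below 0.05, or could hold back that claim until all three do. The two rules have different operating characteristics, and the stated 5% and 90% describe neither of them in full.

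This matters here because the article expects a small effect for each practitioner and says that no data exist on guideline-consistent responses. In that setting one scale significant by chance could readily be read as evidence of effectiveness. A rule chosen after the results are known would not protect against this.

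**Working it through.** **Inputs from the article:** two-sided 5% for every test; 90% power; 543 evaluable per arm; 45% against 55%; three primary scales.

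**Assumption not in the article:** the correlation r between the three test statistics. It is varied from 0 to 0.9, taking the three as equicorrelated normal.

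**1. Reproducing 543 per arm.** For one two-proportion comparison,

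n0 = [1.960·√(2·0.5·0.5) + 1.2816·√(0.45·0.55 + 0.55·0.45)]² / 0.10² = (1.3859 + 0.9017)² / 0.01 ≈ 523.3.

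With the continuity correction,

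n = (n0/4)·[1 + √(1 + 4/(n0·0.10))]² ≈ 543.1.

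The published figure is therefore that of one continuity-corrected comparison at 5%.

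**2. Any one scale suffices.** With no true effect on any scale and independent tests, the chance of at least one false positive is 1 − 0.95³ = 0.143. With correlated tests it is P(at least one |Z| > 1.960):

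| r | Familywise error |
|---|---|
| 0 | 14.3% |
| 0.3 | 13.6% |
| 0.5 | 12.5% |
| 0.6 | 11.8% |
| 0.8 | 9.8% |
| 0.9 | 8.4% |

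**3. All three scales must succeed.** The familywise error does not exceed 5%. Assuming a true effect giving 90% power on each scale, joint power is 0.9³ = 0.729 if independent, and otherwise P(all three Z > 1.960) with each mean at 1.960 + 1.2816:

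| r | Joint power |
|---|---|
| 0 | 73% |
| 0.5 | 78% |
| 0.8 | 83% |
| 0.9 | 85% |

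**4. Adjusted test per scale.** Power at n per arm with continuity correction is

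Φ{[0.10 − 1/n − z·√(2·0.25/n)] / √(0.495/n)}.

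At n = 543, 1/n = 0.00184, √(0.5/543) = 0.03035 and √(0.495/543) = 0.03019.

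- Level 0.05, z = 1.960: (0.09816 − 0.05948)/0.03019 = 1.281, power 90.0% (91.0% without the 1/n term).
- Level 0.05/3 = 0.0167, z = 2.394: (0.09816 − 0.07265)/0.03019 = 0.845, power 80.1% (81.8% without the 1/n term).

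**5. Away from 50%.** The general form of the same formula replaces 0.25 with p̄(1 − p̄) and 0.495 with p1(1 − p1) + p2(1 − p2). At level 0.0167 and 543 per arm (with and without the correction), it gives 84–86% for 60% against 70%, 91–92% for 70% against 80%, and 98–99% for 80% against 90%. The 80% figure is thus a worst case.

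**The case against.** The strongest reply is that the primary question is put for each scale. Three separate conclusions, about work, activity and bed-rest, would each carry a 5% error and 90% power. That reading is possible and would resolve the point if stated, but the article does not state it, and its aim and conclusion ask for one verdict on the package.

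A second reply is that a journal article may leave multiplicity to an analysis plan. That would answer a complaint of missing detail. Here, though, the article sets 5% for every test and sizes the trial on one comparison, so an adjustment made elsewhere would have to be reconciled with both statements.

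Three stronger readings are tempting, and the article does not support them.

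- **Six primary tests.** A reader might add the three ordinal analyses, since both research questions are introduced under the primary outcome, and arrive at about 21%. The article then makes only the first question primary, attaches the primary label to the binomial model alone, and calls the whole-scale approach an alternative analysis. The strict cut-offs are already sensitivity analyses. The 21% also needs correlations that appear nowhere in the article.
- **An unconditional error rate of 12–14%.** This presupposes an any-scale rule, which is not stated, and correlations no higher than about 0.6. One respondent answers all three questions about one vignette, so higher values are possible.
- **90% power for one scale only.** Each scale tested alone at 5% has 90% power, because 45% against 55% was chosen as the most demanding case.

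**Conclusion.** The point stands in conditional form. The article has three co-equal primary comparisons, each at an unadjusted 5%, a sample size for one, and no rule linking them to the overall claim.

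- Under an any-scale rule the familywise error is about 8–14%, for correlations from 0.9 down to 0.
- Under an all-scales rule the error is controlled, but joint power is about 73–85% over the same correlations, given 90% on each scale.

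Neither rule gives the stated 5% and the stated 90% together for the overall conclusion. The ranges rest on an assumed common correlation, and the joint power also on a true effect of the planned size on all three scales. The finding is confined to the three lenient dichotomised comparisons.

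**What to change.** Before the follow-up data are analysed, declare the three lenient dichotomised comparisons (work, activity, bed-rest) one primary family and test them by Holm at an overall two-sided 5%. State that a claim of effectiveness will name the scale or scales that succeed. Restate power as at least about 80% per scale at the first Holm step in the worst case of 45% against 55%, higher when the proportions lie away from 50%, and say that 90% applies only to a single unadjusted scale.

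Naming one lead scale, or requiring all three with the joint power stated, would also close the gap. Holm is preferred because it keeps the three scales on an equal footing, as the article has them.

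The cost is a paragraph in the analysis section and a less favourable stated power. No extra participants or data are needed. By contrast, keeping 90% per scale at level 0.0167 would need 693 evaluable per arm (continuity-corrected), or 693/0.6 = 1155 recruited per arm after the planned 40% loss, against the 900 planned.

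### The baseline-adjusted primary model does not in general estimate the overall difference in proportions that the trial is framed and sized on; the primary estimate should be stated as a standardised risk difference

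*Protocol article*

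**What the plan says.** The Abstract (Methods) says that the analysis of the primary outcome will assess between-arm differences in the proportions of responses classed as guideline-consistent or guideline-inconsistent.

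Sample size calculation sets the size of change that matters: "we defined a change of 10% in reported behaviour between the proportions of practitioners from baseline to the six-months post-intervention follow-up as a clinically meaningful". The target is then put as a comparison of the arms at follow-up: "To show a 10% difference in the proportion of these practitioners who, at the six-month post-intervention follow up", would answer consistently with guidelines. The article takes the least favourable case ("the greatest statistical power is needed when proportions in each group are 45% and 55" per cent) and arrives at 543 analysable participants per arm.

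Data handling and analyses makes a binomial regression of the dichotomised answer the primary analysis and says of it: "This will allow for between-arm differences of the proportions of responses that fall within each category at follow-up to be tested". It adds: "Baseline reported behaviour responses will be included in each model as a covariate". Neither the link nor the effect measure is named. The lenient cut-off is primary and the strict one is a sensitivity analysis.

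**The concern.** The sizing quantity is unconditional: the proportion consistent among all practitioners in one arm minus that in the other. The coefficient for arm in a model that also contains the practitioner's own baseline answer is conditional on that answer. The two can differ, and the baseline answer is likely to be a strong predictor.

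Under an identity link, a main-effects model assumes one common gain in percentage points. A practitioner already consistent at baseline may have little room to improve. If so, the common-gain assumption fails, and maximum likelihood gives most weight to the stratum with the smallest variance, which is the one near the ceiling. Under a logit link the coefficient is a conditional log odds ratio. It is a legitimate measure, but it is not in percentage points.

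At stake is how the primary result can be read. The article calls 10 points meaningful, but the estimate its model yields may be on another scale, or may be smaller than the overall difference.

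**Working it through.** **1. The plan's own figure.** Inputs from Sample size calculation and Data handling and analyses: 45% v 55%, two-sided 5%, 90% power.

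n = [1.960·√(2·0.5·0.5) + 1.2816·√(0.45·0.55 + 0.55·0.45)]² / 0.10² = (1.3859 + 0.9017)² / 0.01 = 523.3 per arm.

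With continuity correction: (523.3/4)·[1 + √(1 + 4/(523.3·0.10))]² = 543.1.

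The stated 543 is reproduced. It is a calculation for an unadjusted difference between two overall proportions.

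**2. Assumed scenarios.** The article gives neither the baseline proportion consistent nor its association with follow-up, so both are assumed. Each scenario is built for a true overall difference of 10 points; the rounded inputs of (a) give 10.15.

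| | Consistent at baseline | Control: inconsistent / consistent at baseline | Intervention: same order | Overall, control v intervention |
|---|---|---|---|---|
| (a) | 45% | 16% / 80% | 32% / 83% | 44.8% v 55.0% |
| (b) | 50% | 20% / 90% | 37% / 93% | 55% v 65% |
| (c) | 70% | 25% / 92% | 50% / 95.6% | 71.9% v 81.9% |

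Overall differences: (a) 0.55·16 + 0.45·3 = 10.15; (b) 0.5·17 + 0.5·3 = 10.0; (c) 0.3·25 + 0.7·3.6 = 10.02 points.

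**3. Identity link.** The common-difference estimate is close to an average of the stratum differences with weights (stratum share)/(mean of p(1−p) over the two arms).

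- (a) weights 0.55/0.176 = 3.125 and 0.45/0.1506 = 2.989; (3.125·16 + 2.989·3)/6.114 = 9.6 points.
- (b) weights 0.5/0.1966 = 2.544 and 0.5/0.0776 = 6.447; (2.544·17 + 6.447·3)/8.991 = 7.0 points.
- (c) weights 0.3/0.2188 = 1.371 and 0.7/0.0578 = 12.104; (1.371·25 + 12.104·3.6)/13.475 = 5.8 points.

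The exact large-sample maximum-likelihood limits are 9.7, 7.1 and 5.8 points. In (c) the stratum with 70% of practitioners carries 12.104/13.475 = 90% of the weight.

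**4. Logit link.** The conditional odds ratios are 1.85, 2.07 and 2.55. The overall odds ratios from the table in step 2 are 1.50, 1.52 and 1.77.

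**5. Standardised difference.** Fit the logistic model with arm and baseline response, predict every participant under each arm, average, and subtract. The large-sample result is 10.0 to 10.2 points across the three scenarios, equal to the true overall difference in each.

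**6. Intervals and power.** In 600 simulated trials of 543 per arm for each scenario, the identity-link 95% CI covered the true overall difference in 94%, 70% and 32% of trials in (a), (b) and (c). Coverage for the standardised difference was 93% to 95%. Power was 97%, 93% and 91% with the identity link, against 99%, 99% and 100% standardised. With no effect (baseline set-up of (a)), both tests rejected in 6% of trials.

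**7. Where the issue vanishes.** With the same gain in both strata (16% / 80% v 26% / 90%) the identity link returns exactly 10.0. With a weak baseline association (control 30% / 63%) it returns 9.95 to 10.0.

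**The case against.** The strongest case against the point is that the sentence on the primary model speaks of testing. No effect is the same null hypothesis under every link, the simulated error rate is the same for both methods, and identity-link power stays above the planned 90%. Binomial regression includes the risk-difference model. Near the only case the article sizes on, that model is off by about half a point. The larger gaps come from (b) and (c), which assume higher proportions and very unequal gains (3 v 17 and 3.6 v 25 points). An article may also leave the link to a fuller document.

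Most of this stands. The test is valid, and silence on the link is not in itself a fault. What remains is that the article commits to a specific adjusted model while framing its question, in the Abstract and the sample size, as an overall difference in proportions. The 45% v 55% case was chosen as the most demanding, in the absence of data, and is not a forecast. With the lenient cut-off primary, higher proportions are plausible.

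A reader might infer more than the documents support:

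- That no link can return the overall difference. This is wrong: the identity link does so exactly under a constant risk difference.
- That one 10-point effect would be reported as about 6 or about 17 points depending on the link. That pair arises in one assumed case (45% consistent at baseline, control 15% / 81.7%, common odds ratio): a log-link risk ratio of 1.129 gives 0.129·45 = 5.8 points, and an odds ratio of 2.03 applied to 45% gives 17.4. The identity link there gives 9.8. The article plans no such conversion.
- That the result fails a 10-point decision rule. The article states none; 10% is the meaningful change used for sizing.

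**Conclusion.** The point holds as a limited one about estimation. The arm coefficient from the baseline-adjusted model is not, in general, the overall difference in proportions that the article asks about. Under ceiling effects an identity-link estimate can fall short of a true 10 points: slightly near the design case (9.7, against 10.15 with those inputs), and by about 3 and 4 points at 55% v 65% and 72% v 82%. A logit coefficient is on a different scale altogether. The size rests on assumed baseline prevalence and association and on unequal gains across baseline strata; with equal gains the identity-link gap is nil, and with a weak association it is negligible. Validity of the planned test and the sample size are not in question. The change is a worthwhile, inexpensive improvement, not the repair of an invalid analysis.

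**What to change.** In Data handling and analyses, keep the baseline-adjusted model and specify it as a logistic regression on arm and the baseline response on the same scale. State that the primary estimate for each of the work, activity and bed-rest scales is the standardised between-arm difference in the proportion guideline-consistent at six months. To obtain it, predict each analysed participant's probability under both arms, average within each, and take the difference, with a 95% CI from a robust delta-method or bootstrap standard error. Use the same method for the strict cut-off.

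The cost is a sentence or two of text and a short computation after the regression. No new data are needed. An identity-link risk difference would also be on the right scale, but it moves away from the overall difference when gains are unequal across baseline strata.
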